#### Control group/sham laser acupuncture group

2.3.2

Subjects in the control group will accept the same number of sessions and interval times as the intervention group. Sham LA treatment will be applied without any laser power output. There will be no differences in observation, feeling, or listening between the two groups during the procedure. Hence, all patients in both groups will be blinded to group selection.

### Participants

2.4

#### Sample size

2.4.1

The necessary number of subjects required for our study is based on a previous study of the effects of LLLT for CTS.^[22]^ The sample size was calculated with a power of 80% (1 – β = 0.8), statistical significance (α = 0.05) of 95% and a dropout rate of 20%. As a result, this study will require at least 40 wrists.

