**Methods::**

This study protocol is a prospective double-blind randomized controlled trial. Forty subjects aged 20 to 80 years old and diagnosed as having mild to moderate CTS will be randomly assigned to the intervention group (real LA, 3-sessions a week for 2 weeks) and control group (sham LA, 3-sessions a week for 2 weeks). All subjects will be asked to wear night splints as the fundamental management approach. The laser parameters will include a wavelength of 808 nm, power output of 300 mW and power density of 300 mW/mm^2^, with ten seconds of treatment for each acupuncture point (PC4, PC6, PC7, PC8, LI4, LI10, LI11, HT3, HT7, and LU10). Sham LA treatment will be applied without any laser power output. The primary outcome will be based the Boston Carpal Tunnel Syndrome Questionnaire and secondary outcomes included a visual analog scale, cross sectional area of median nerve by sonography and electrophysiological test before interventions and after 2, 4, 8, 12 weeks postintervention.

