### Study design

2.2

This study protocol was designed as a prospective, randomized, double-blind, controlled trial according to the CONSORT 2010 statement (Fig. 1)^[27]^ and will be conducted at Tri-Service General Hospital in Taiwan in 2019. The recruited participants will be randomly assigned to the intervention group (real LA) or control group (sham LA) via computer-generated random numbers (1:1 ratio) using Microsoft Excel. If the patients are diagnosed with bilateral CTS, both wrists will be assigned to the same group. All subjects will wear night splints at least 8 h per night through the whole study period as the fundamental management approach.^[28]^ The LA device (“TRANS” Laser Phototherapy Device, TRANSVERSE INDUSTRIES CO., LTD, Taiwan) is like a pen (Fig. 2). A semiconductor was made of gallium–aluminum–arsenide (Ga–Al–As) with a wavelength of 808 nm, power output of 300 mW and power density of 300 mW/mm^2^ (following the guidelines of Jekins and Carroll).^[24,29]^ Real LA and sham LA will be applied by the same physician who is a licensed Chinese medicine practitioner in Taiwan. The ten acupuncture points include PC4 (Ximen), PC6 (Neiguan), PC7 (Daling), PC8 (Laogong), LI4 (Hegu), LI10 (Shousanli), LI11 (Quchi), HT3 (Shaohai), HT7 (Shenmen), LU10 (Yuji) (Fig. 2 and Fig. 3). Some of these points have used in other CTS studies.^[30,31]^ These acupoints are located according to the WHO Standardized Acupuncture Point Localization guidelines.^[32]^

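### The abstract randomises 40 subjects but section 2.4.1 requires 40 wrists; with patients randomised whole, the wrist target may carry less than the stated 80% power

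*Protocol article*

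**What the plan says.** The Abstract (Methods) gives the size in people: "Forty subjects aged 20 to 80 years old and diagnosed as having mild to moderate CTS will be randomly assigned".

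Section 2.4.1 (Sample size) sets out to give the same quantity, beginning "The necessary number of subjects required for our study", but it ends in a different unit: "this study will require at least 40 wrists". The inputs it lists are 80% power, α = 0.05, 20% dropout and a pointer to an earlier study of low-level laser therapy. It states no effect size, standard deviation, share of bilateral patients or between-wrist correlation.

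Section 2.2 (Study design) randomises participants 1:1 and adds: "If the patients are diagnosed with bilateral CTS, both wrists will be assigned to the same group". Section 2.6 (Statistical analysis) compares the groups with an independent t test, two-tailed at .05.

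**The concern.** Subjects and wrists are interchangeable only if every patient has one affected wrist, and section 2.2 expressly provides for patients with two. The article therefore states two targets, and section 2.4.1 changes unit within one paragraph.

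The wrist target also does not match the unit of randomisation. A bilateral patient is a cluster of two within one arm. Two wrists of one person usually carry less information than two wrists of two people, because they share the patient, the allocation and the self-report. If the 80% was worked out as though 40 wrists were 40 independent units, a trial that recruits 40 wrists could satisfy section 2.4.1 with as few as 20 independent units. That cannot be repaired once recruitment has closed.

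**Working it through.** **Inputs from the article.** Power 80%, α = 0.05 and dropout 20% (section 2.4.1); two-tailed tests and an independent t test (section 2.6); 1:1 allocation of patients with both wrists kept together (section 2.2).

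**Assumed inputs, not in the article.** Share of bilateral patients b (0 to 100%) and between-wrist correlation ICC (0.3 to 1.0 tabulated).

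**Step 1: range of the two targets.** Forty wrists is 40/2 = 20 patients if all are bilateral and 40 if none is. Forty subjects is 40 to 80 wrists.

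**Step 2: what 40 fits.** A forward reproduction is impossible without an effect size, so I solved backwards. 40 × (1 − 0.20) = 32 evaluable, or 16 per arm. With the normal approximation, d = (1.960 + 0.842) × √(2/16) = 0.99. With the t test, 16 per arm and 80% power give d = 1.02. As a check, the normal approximation at d = 1.0 gives 2 × 2.802² = 15.7, rounded up to 16 per arm; 32 in total; 32/0.8 = 40. So 40 is what a plain two-group calculation on independent units returns at d of about 1, with no design effect.

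**Step 3: design effect if those 40 units are wrists.** With wrists weighted equally, DE = 1 + (m′ − 1) × ICC, where m′ = (1 + 3b)/(1 + b). The effective number per arm is 16/DE. Power is for the two-sided t test at d = 1.024, read as an analysis that respects the clustering.

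| Bilateral share (patients for 40 wrists) | ICC | DE | Effective n per arm | Power |
|---|---|---|---|---|
| 0% (40) | any | 1.00 | 16.0 | 80.0% |
| 25% (32) | 0.3 | 1.12 | 14.3 | 75.0% |
| 25% | 0.5 | 1.20 | 13.3 | 71.9% |
| 25% | 1.0 | 1.40 | 11.4 | 64.6% |
| 50% (about 27) | 0.3 | 1.20 | 13.3 | 71.9% |
| 50% | 0.5 | 1.33 | 12.0 | 66.9% |
| 50% | 1.0 | 1.67 | 9.6 | 56.2% |
| 100% (20) | 0.3 | 1.30 | 12.3 | 68.1% |
| 100% | 0.5 | 1.50 | 10.7 | 61.2% |
| 100% | 1.0 | 2.00 | 8.0 | 47.9% |

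At ICC 0, power is 80% for every bilateral share.

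**Step 4: sensitivity to weighting.** With one value per patient at ICC 1, the effective number per arm is the number of patients, 16/(1 + b). For b = 25% this is 12.8 per arm and power of about 70%, not 65%. For b = 50% it is 10.7 and about 61%, not 56%. With all bilateral the two weightings agree.

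**Step 5: the abstract's target.** Forty patients less 20% is 32 evaluable patients, 16 per arm. With one value per patient, power is 80% at the same d.

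**The case against.** The strongest reply is that the two figures can both be true. Section 2.4.1 sets a minimum, and forty subjects with at least one affected wrist each supply at least 40 wrists. The Abstract is the only place that says how many are randomised, and at that number the power is kept with a patient-level analysis. The article gives no rule for when enrolment stops. This stands as a possible reading, and it is the one the fix confirms. It does not remove the inconsistency, because section 2.4.1 is where the size is justified and as worded it is also met by 20 patients.

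A reader might go further and infer that 40 wrists definitely fail to deliver 80%. The documents do not support that. The standardised difference is back-solved on the premise of independent wrists, so the shortfall depends on that premise. A clustering allowance is neither mentioned nor excluded, and a condensed article may leave it to the full protocol. The bilateral share and the correlation are not given. The true power cannot be computed from what is shown.

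A reader might also count patient-level dropout as a further loss, since a bilateral patient who leaves takes two wrists. If dropout is unrelated to bilaterality, losing 20% of patients still loses 20% of wrists on average, so there is no additional expected shortfall.

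**Conclusion.** The inconsistency of units is explicit and stands without any assumption: the size is stated once in subjects and once in wrists, the two can differ by a factor of two, and the wrist is not the unit randomised.

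The effect on power is conditional. It needs three things together: 40 wrists is the operative target, no clustering allowance was made, and some patients contribute two positively correlated wrists. Power is then below 80%, by the amounts tabulated for ICC 0.3 to 1.0; correlations below 0.3 cost less. The lower ends for 25% and 50% bilateral also rest on equal weighting of wrists. All of these figures illustrate the size of the risk at d of about 1.02; none is an estimate of this trial's power.

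The point should be settled before recruitment ends, because it decides how many patients are enrolled.

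**What to change.** State one target in the Abstract and in section 2.4.1, expressed in patients: 40 patients, 20 per arm, as the Abstract already has it, and say that the patient is the unit of the power calculation. This costs one sentence and needs no enrolment beyond what the Abstract promises.

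If 40 wrists is really the target, restate the power in section 2.4.1 after a design effect, give the assumed bilateral share and between-wrist correlation, and label the result as conditional on them. The cost is then a less favourable power figure or more wrists. The percentages above should not be copied into the protocol, since they rest on inputs assumed here; the sponsor should use its own.

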#### Inclusion and exclusion criteria

2.4.2

Participants aged 20 to 80 years diagnosed with mild- to -moderate CTS with clinical symptoms for at least 3 months and confirmed by electrophysiological testing will be enrolled. The definition of clinical symptoms/signs, and inclusion and exclusion criteria are summarized in Table 1. Patients will be excluded if they meet one of the exclusion criteria. The diagnosis and the grades of CTS are based on electrophysiological classification (Table 2).^[34,35]^

**Table 1 T1:**
[figure not shown]
Summarization of inclusion and exclusion criteria.

**Table 2 T2:**
[figure not shown]
Electrophysiological classification of diagnosis and grades of carpal tunnel syndrome.

### Outcome measurements

2.5

The same physiatrists who are blinded to the patients’ randomization will perform all the measurements for all participants of both groups before intervention and 2, 4, 8, and 12 weeks after intervention.

#### Primary outcomes

2.5.1

##### The Boston carpal tunnel questionnaire (BCTQ)

2.5.1.1

BCTQ is a disease-specific measurement of self-reported symptom severity and functional status for CTS.^[36]^ One is the minimum score and five is the maximum score on each symptom severity scale (SSS) (11 items) and functional status scale (FSS) (8 items). The total scores of SSS and FSS range from 11 to 55 and 8 to 40, respectively. We will use the Chinese version of the BCTQ, which had been corrected for reliability and validity.^[37]^

#### Secondary outcomes

2.5.2

##### Visual analog scale (VAS)

2.5.2.1

We will use VAS to measure the severity of digital pain or paresthesia/dysesthesia induced by CTS within 1 week before treatment and upon each follow-up time point.^[38]^ Zero is the minimum score for pain and ten is the maximum score for pain.^[39]^

##### Electrophysiological test

2.5.2.2

Following the protocol, the electrophysiological test was developed by the American Academy of Neurology with SierraWave, Cadwell (USA).^[34]^ The setting of the active recording and stimulator is described in Table 2.^[40]^ Each measurement from the electrophysiological test will be made three times and averages of the values obtained will be determined for analysis.

##### Ultrasonography of median nerve

2.5.2.3

Cross sectional area (CSA) of the MN at the proximal inlet of carpal tunnel was measured by using ultrasonography (MyLab^TM^ 25Glod, Esaote, Genova, Italy) in our previous study.^[40]^ CSA represents the swelling of MN with high validity for post-treatment evaluation.^[28,38,41]^ Each measurement from ultrasonography will be made three times and the averages of the values obtained will be calculated for analysis.

### Statistical analysis

2.6

All statistical analyses will be performed with IBM SPSS Statistics Version 24. All data will be presented as mean ± standard error. The pair *t* test will be used to evaluate and compare before and after treatments within each study group. The independent *t* test and chi-square will be used to evaluate and compare before and after treatments between two groups. All statistical tests will be two-tailed and a *P*-value less than .05 is considered to be a statistically significant difference.

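### The between-arm comparison is an unadjusted t test, on follow-up or change scores (the text does not say which), although baseline is collected; a baseline-adjusted analysis would usually be more precise

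*Protocol article*

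**What the plan says.** Section 2.6 (Statistical analysis) gives two sentences on testing. Within each arm, a paired *t* "test will be used to evaluate and compare before and after treatments within each study group". Between arms, an independent *t* "test and chi-square will be used to evaluate and compare before and after treatments between two groups". "All statistical tests will be two-tailed", at the 0.05 level. The section names no covariate, ANCOVA or repeated-measures model.

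Section 2.5 (Outcome measurements) states that blinded assessors "will perform all the measurements for all participants of both groups before intervention", and again at 2, 4, 8 and 12 weeks. The primary outcome in Section 2.5.1 is the Boston questionnaire, with a symptom score from 11 to 55 and a function score from 8 to 40. Both are numeric, and both are available at baseline.

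Section 2.4.1 (Sample size) uses 80% power and a 20% dropout allowance and concludes that "this study will require at least 40 wrists". It gives no effect size or standard deviation. Section 2.2 puts both wrists of a bilateral patient in the same arm.

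**The concern.** The between-arm sentence can be read in two ways. It may mean separate tests on the scores before treatment and at follow-up, or one test on the before-to-after change. The two readings can give different estimates and different precision from the same data, so the choice should be fixed in advance.

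Neither reading adjusts for baseline. A test on follow-up scores gives the baseline value a weight of 0, and a test on change gives it a weight of 1. With equal variance before and after, the efficient weight is the correlation r, which ANCOVA estimates from the data. In a trial of about 16 to 20 units per arm, the difference in precision can matter, and so can chance imbalance at baseline.

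**Working it through.** **1. Inputs.** From the document: 40 wrists, 20% dropout, 1:1 allocation, 80% power, two-sided 0.05. Evaluable units: 40 × 0.8 = 32, or 16 per arm. Assumed: the correlation r between baseline and follow-up (range 0 to 0.8), equal variance before and after, and independent units.

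**2. The plan's own figure.** The 40 cannot be reproduced, because no effect size or SD is given. Solving backwards, a standardized difference of 1.0 needs 2 × (1.96 + 0.84)² / 1.0² = 15.7, so 16 per arm or 32 in total, and 32 / 0.8 = 40. With the exact t distribution, 16 per arm has 80% power at 1.02 SD. That effect is used below as a common reference.

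**3. Formulas.** Variance of the treatment difference relative to the follow-up-score t test, with N = 32:
- follow-up score: 1
- change score: 2(1 − r)
- ANCOVA: (1 − r²) × (1 + 1/(N − 4)) = (1 − r²) × 1.036, tested on 29 instead of 30 degrees of freedom

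The CI ratio is the square root of the variance ratio times the ratio of t quantiles, 2.0452 / 2.0423.

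**4. One line in full, r = 0.5.** ANCOVA variance: 0.75 × 1.036 = 0.777. Change-score variance: 2 × 0.5 = 1.00. CI ratio against either t test: √0.777 × 1.0014 = 0.883, about 12% narrower.

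**5. Results, 16 per arm, effect 1.02 SD.**

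| r | Variance, change | Variance, ANCOVA | CI ratio vs follow-up | CI ratio vs change | Power, follow-up | Power, change | Power, ANCOVA |
|---|---|---|---|---|---|---|---|
| 0 | 2.00 | 1.036 | 1.019 | 0.721 | 80% | 50.9% | 78.5% |
| 0.2 | 1.60 | 0.994 | 0.999 | 0.789 | 80% | 60.1% | 80.1% |
| 0.3 | 1.40 | 0.943 | 0.972 | 0.822 | 80% | 65.8% | 82.2% |
| 0.5 | 1.00 | 0.777 | 0.883 | 0.883 | 80% | 80.0% | 88.8% |
| 0.7 | 0.60 | 0.528 | 0.728 | 0.940 | 80% | 95.1% | 97.1% |
| 0.8 | 0.40 | 0.373 | 0.612 | 0.967 | 80% | 99.3% | 99.6% |

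A simulation of 8,000 trials at each of r = 0, 0.3, 0.5 and 0.7 gave ANCOVA power of 78.5%, 82.4%, 88.7% and 96.9%, in line with the table.

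**6. Break-even.** Against the follow-up-score test, ANCOVA starts to gain at r of about 0.19 with 16 per arm and 0.17 with 20 per arm. Against change scores it gains at every r shown.

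**7. Baseline imbalance.** With 16 per arm the SD of the baseline difference is √(2/16) = 0.354 SD units, so a difference above 0.3 SD arises in about 40% of randomisations. Given a 0.3 SD imbalance and r = 0.5, the expected follow-up-score difference shifts by 0.5 × 0.3 = 0.15 SD and the expected change-score difference by (0.5 − 1) × 0.3 = −0.15 SD.

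**The case against.** **The unadjusted test is valid.** Under randomisation, and with independent units, a t test on follow-up or change scores is unbiased and keeps its nominal error rate, and chance imbalance is already reflected in its standard error. This stands: the point concerns efficiency and an unclear specification.

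**The gain depends on an unknown r.** This also stands. At r = 0.3 the gain over follow-up scores is about 3% in CI width. At r = 0.8 the gain over change scores is also about 3%. Adjustment is not strictly free either: it costs one degree of freedom and a variance penalty of 1/28 = 3.6% at N = 32 (1/36 = 2.8% at N = 40).

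**A reader might infer that the plan ignores baseline and significance-tests it.** The text does not establish this. The preceding sentence on paired tests makes a change-score reading equally natural, and then baseline is used, though with a fixed weight.

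**A reader might infer that each t test drops patients not seen at that visit.** The document does not say so. The 20% is an allowance in the sample size, and the handling of missing visits may sit in an analysis plan that is not shown. Single-visit ANCOVA would not recover such patients in any case, so this forms no part of the point.

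**Details may be in a fuller plan.** Covariates often are. Here, however, the article itself states the between-arm test, and that stated choice is what is questioned.

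**Conclusion.** The point holds in a limited form. Section 2.6 fixes an unadjusted independent t test and leaves open whether it is on follow-up or change scores. On both readings, a baseline value that is already collected is not used efficiently. At an assumed r of 0.5, adjustment narrows the CI by about 12% and raises power from 80% to about 89%. At other values the gain depends strongly on which t test was meant.

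These figures assume equal variances, 32 independent units and a reference effect of 1.02 SD solved back from the stated size. If wrists are analysed and some patients contribute two, the units are not independent, so the power levels should not be taken as the trial's actual power. The improvement is worth making, but it does not invalidate the planned comparison.

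**What to change.** In Section 2.6, replace the between-arm t test for each continuous outcome with one of these:
- ANCOVA with the baseline value as covariate at each of weeks 2, 4, 8 and 12; or
- one linear mixed model with arm, visit, arm-by-visit and baseline value.

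Include a patient random effect, and model wrist within patient if wrists are the unit of analysis. Report the adjusted between-arm difference with its 95% CI. The protocol names no primary visit, so the wording should refer to the stated visits.

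The cost is a change of analysis wording made before the data are unblinded. No further data are needed. The statistical cost is one degree of freedom, a 3–4% variance penalty, and a slight loss against a follow-up-score test if r is below about 0.2.

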## Discussion

3

To the best knowledge, the present study is the first prospective, randomized, double-blind, controlled trial to investigate the therapeutic effect of LA for mild to moderate CTS.

Previous studies indicated that LA therapy is a noninvasive technique with a painless, safe procedure and requires less time compared with needle-based acupuncture.^[42–44]^ Although the true effect of LA for CTS is uncertain based on a single small crossover study,^[17]^ current research of LLLT for CTS points to favorable short-term effects. A recent systematic review has shown that the effectiveness of LLLT can be maintained up to 5-weeks, but cannot be maintained upon 5 to 7-week follow-up. Moreover, reports of 3 to 6-month follow-ups provide limited evidence.^[24]^ Hence, a 3-month follow-up in our trial can adequately evaluate LA for CTS.

LA means applying LLLT to acupuncture points. Although the definite mechanism of LA is unclear, a combined effect of LLLT and traditional acupuncture is expected. In our opinion, LA not only requires less time than traditional LLLT, but also has a meridian treatment effect. The near infrared light from LLLT is absorbed by mitochondria, thus inducing the change of the cellular respiratory chain involving nitric oxide, reactive oxygen species and cyclic adenosine monophosphate (cAMP).^[10]^ One theory called the Acupoint Energy System states that acupoints are constituted by cells with more mitochondrial adenosine triphosphate (ATP).^[45]^ Therefore, the mechanism of LA seems to be associated with mitochondria, but further research is still needed.

In conclusion, LA is expected to be effective for the treatment of mild to moderate CTS and the results of this study will reveal its real benefit through sonography and electrophysiologic measurements.
